
### Data analysis

#### Primary analyses

With 24 clusters, individual-level analyses of trial outcomes are possible. Mixed-effect linear regression models will be used with clusters and participants specified as random effects to take account of the clustering at the facility level and the repeated measures within participants. We will create separate models for alcohol and depression. The analysis will be intention-to-treat. For cluster RCTs, the dropout of clusters is rare. We will consider using multiple imputations to account for missing responses of participants at follow-up in order to reflect the true overall uncertainty of the estimated effect sizes. The two primary outcomes will be ascertained at three time points for each participant. This repeated measure feature will be used to estimate the intervention effects and 95% confidence intervals for the two primary outcomes at 12 months for three contrasts (the contrast between the Dedicated arm and TAU arm, the contrast between the Designated arm and TAU, and the contrast between the two active arms (Dedicated versus Designated), which will serve as the main comparison). Our primary analysis of outcomes will include adjustment for stratification variables. No adjustment for multiplicity will be made since the trial outcome will be determined by the overall significance of the group (intervention) effect. A similar approach will be adopted to estimate the intervention effects and 95% confidence intervals for the secondary outcomes.

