### Interventions

#### Control: TAU arm

Participants recruited from facilities assigned to the control arm will receive the standard package of care when a health provider suspects a patient may have a CMD. This standard of care involves asking patients about their mood, stressors and their use of alcohol when patients present for HIV or diabetes care. If a patient discloses difficulties in these areas, the patient may be given lifestyle advice and provided with a referral to an on-or off-site mental health nurse or social worker for further assessment [45]. We have previously found that the implementation of this standard of care varies considerably among facilities. Consequently, we will provide all participants recruited in TAU facilities with a resource guide that contains mental health and substance abuse services within their health sub-district and a referral to a service provider of their choice.

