Therefore, it is intended that participants in both intervention arms will receive the same counselling programme, but that the job scope of the person delivering the counselling will differ. In facilities assigned to the dedicated arm, one CHW will be added to each facility (eight in total). This CHW will be tasked with providing the counselling programme to patients with HIV and those with diabetes, but will have no other formal chronic disease-related duties. If they have spare capacity, they may assist with administrative and other tasks for the chronic disease care team, but their priority will be the delivery of project MIND’s mental health counselling package. Although these CHWs will be employed as part of the study, their salaries and conditions of employment will match those of the CHWs in the designated arm. In the designated arm, we will identify eight CHW (one per facility) already employed as facility-based counsellors who will be designated to provide the counselling programme to patients with HIV and those with diabetes in addition to their usual chronic disease-related counselling responsibilities. Both dedicated and designated CHWs will be required to complete a time and motion tool that captures their activities and the time spent on each activity on a daily basis. Activities may include mental health counselling, administrative tasks, participation in supervision or training, and other chronic disease activities, which they will be required to specify. This will allow for an exact understanding of their daily activities to be developed.

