#### Economic/costing measures

Full economic costs will be assessed from a societal (i.e. provider and patient) perspective within each of the three study arms. For the provider perspective, costs include the costs of the dedicated/designated approach, the costs of chronic disease (HIV/diabetes) care, and the costs of a range of referral services (e.g. referral for TB treatment or inpatient care). While TAU does not include any counselling costs, our inclusion of chronic disease and referral costs for each of the three arms ensures that any potential changes to a broader range of costs is captured. Provider costs will be estimated using a combination of ingredients and step-down methods. A time and motion study will capture the time spent by dedicated or designated CHWs on their daily activities. This will enable an assessment of excess capacity (hypothesized to occur in the dedicated CHWs) and economies of scope (hypothesized to occur in the designated CHWs). Ultimately, a provider cost per patient year will be computed for each study arm/chronic disease.

In the patient perspective, costs include travel costs, the opportunity costs of travel and waiting times, productivity gains or losses and out-of-pocket payments (such as food purchased during a clinic visit, user fees for a private hospital stay, and the costs of additional over-the-counter medicines). Using patient questionnaires, these data will be collected for all of the health services utilized by the patient during the month preceding the interview for the baseline and follow-up assessments (including additional mental health services). We will extrapolate these data in order to calculate a patient cost per patient year for each study arm/chronic disease. In addition, we will collect a range of socioeconomic and demographic data to enable an assessment of patient costs and catastrophic expenditure by socioeconomic status.

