Despite these strengths, we anticipate some challenges to trial implementation. Recruitment of individual participants may pose challenges given the reliance on facility staff for the initial identification of suitable patients to approach for screening. To address this potential challenge to recruitment, we have developed a PHC facility engagement strategy that includes regular meetings with facility management, implementation readiness workshops to build a shared commitment to the study, joint trouble-shooting of challenges, and regular feedback of study progress at facility meetings. Second, retention of participants in a three-session intervention and through the lifespan of the study may pose some challenges. We have a comprehensive strategy to limit attrition (including reimbursement of transport costs) that has been used in other studies where we have obtained more than 80% follow-up rates [74]. Third, there are other ongoing initiatives to integrate and strengthen PHC services in the province; these other initiatives and contextual differences between facilities may affect study findings. We will collect contextual information and information on other service improvement initiatives regularly from each clinic in order to account for any additional bias. Another potential challenge relates to the quality of counselling provided by CHWs given that CHWs may have low levels of mental health literacy. Although the quality of counselling has a significant influence on the proposed outcome, in order to enhance the quality of care in both of the intervention arms, we plan to monitor the quality and idelity of counselling closely. We also plan to interview participants about their experiences of counselling. Through monitoring and participant feedback, we will learn about the amount of training and supervision needed to develop mental health care competencies among CHWs. This information is likely to be relevant for the implementation of other health programmes involving CHWs.

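### With one facility variance for all arms and visits, the main Dedicated-versus-Designated interval would be too narrow if counsellors differ, because each active facility has a single counsellor and TAU has none

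*Protocol article*

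**What the plan says.** Under Primary analyses, the protocol article specifies mixed-effect linear models over three visits with "clusters and participants specified as random effects to take account of the clustering at the facility level". It mentions no counsellor term, no facility variance that differs by arm and no facility-by-time effect. It promises 95% intervals at 12 months for three contrasts and singles out "the contrast between the two active arms (Dedicated versus Designated), which will serve as the main comparison". It declines a multiplicity adjustment because "the trial outcome will be determined by the overall significance of the group (intervention) effect".

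The section on the two intervention arms assigns one counsellor to each active facility. Eight CHWs are newly placed in the Dedicated arm, and for the Designated arm "we will identify eight CHW (one per facility) already employed as facility-based counsellors". TAU participants get a resource guide and a referral. The costing section confirms the contrast: "While TAU does not include any counselling costs". The Discussion accepts that "the quality of counselling has a significant influence on the proposed outcome". The sample-size section uses a single ICC of 0.030 for all arms.

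**The concern.** Within an active facility every counselled patient has the same counsellor, so counsellor and facility are completely confounded. The facility random effect does absorb counsellor variation, so the missing counsellor term is not itself the fault. The difficulty is that the same variance is applied where counsellors cannot contribute: in TAU, and at baseline in every arm.

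If counsellors differ in effectiveness, two things follow. Pooling over arms averages the larger active-arm variance with the smaller TAU one. Pooling over visits treats an effect that begins after baseline as if it had always been present, so it is not counted in the uncertainty of the change from baseline. Both shorten the interval for the contrast between the two active arms, which is the contrast on which the trial was sized.

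**Working it through.** **Inputs from the protocol article.** 8 facilities per arm; ICC 0.03; AUDIT difference 3 with SD 6.5; CES-D difference 5 with SD 10; two-sided 5% and 90% power; 20 completers per service per facility. The sample size is built on separate HIV and diabetes analyses (m = 20); pooling the services gives m = 40. Both are shown.

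**Assumed.** Counsellor variance v, as a share of total person variance, of 0.01 to 0.05; equal cluster sizes; no covariates; within-person correlation about 0.5 in the three-wave check.

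**The plan's own figure.** Design effect 1 + 19 × 0.03 = 1.57.
- AUDIT: 2 × (6.5 × 3.2415 / 3)² = 98.65 per arm; × 1.57 / 20 = 7.74, so 8 clinics.
- CES-D: 2 × (10 × 3.2415 / 5)² = 84.06; × 1.57 / 20 = 6.60, so 7 clinics.

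Both match the article.

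**Single time point.** Variance of a facility mean, in units of the total person variance:
- active: A = 0.03 + v + 0.97/m
- TAU: T = 0.03 + 0.97/m
- pooled: P = (2A + T)/3

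The ratio of the SE used to the true SE is √(P/A) for the main contrast and √(2P/(A + T)) for active versus TAU. Example with m = 40 and v = 0.03: A = 0.08425, T = 0.05425, P = 0.07425. The main ratio is √0.881 = 0.939 and the TAU ratio √1.072 = 1.035. On the AUDIT scale the main SE is 0.886 where 0.943 is needed.

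| m | v | main SE ratio | TAU SE ratio | main type I error (t, 21 df) |
|---|---|---|---|---|
| 20 | 0.01 | 0.981 | 1.010 | 5.4% |
| 20 | 0.03 | 0.953 | 1.026 | 6.1% |
| 20 | 0.05 | 0.933 | 1.039 | 6.7% |
| 40 | 0.01 | 0.974 | 1.014 | 5.5% |
| 40 | 0.03 | 0.939 | 1.035 | 6.5% |
| 40 | 0.05 | 0.917 | 1.051 | 7.0% |

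Type I errors are simulated. Separate runs of the last setting gave 7.0% to 7.1%, and the highest figure obtained over the whole range was 7.4%. The overall three-arm test stayed at 5.0% to 5.2%. Taking the variance from the 16 active clinics on 14 df gave 4.9% to 5.1%.

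**If TAU facilities also vary.** Give TAU extra facility variance. With v = 0.02 and 0.02 extra in TAU, both ratios are 1.000. With v = 0.02, 0.05 extra in TAU and m = 20, the main ratio is 1.050 and the TAU ratio 0.978, so the direction reverses.

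**Three waves, time-constant intercepts, counsellor effect only after baseline.** For change from baseline the facility and participant intercepts cancel. The model variance of a contrast is about 4σ²/(8m), with σ² = 0.97/2 = 0.485. The true variance adds 2v/8 for the main contrast and v/8 for a TAU contrast. With m = 40 and v = 0.03:
- model: 4 × 0.485 / 320 = 0.00606
- main, true: 0.00606 + 0.0075 = 0.01356; SE ratio √(0.00606/0.01356) = 0.67; simulated coverage 81.5%
- TAU, true: 0.00606 + 0.00375 = 0.00981; SE ratio 0.79; simulated coverage 86.9%

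For v from 0.02 to 0.05, main coverage runs from 90% down to 83% (m = 20) and from 85% down to 74% (m = 40). For the TAU contrasts it is 92% to 89% and 90% to 84%. Here the TAU intervals are too narrow as well.

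**The case against.** Four points on the other side have weight.

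First, the article does not say that the facility variance is equal across arms, and the covariance structure may be settled in an analysis plan that is not shown. That stands as a caution. Still, the article does name its random effects, and those it names separate neither arms nor visits.

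Second, a reader might infer that the main interval is too narrow and the TAU intervals too wide as a matter of fact. The documents do not support this. No counsellor ICC is given. For TAU the article says "We have previously found that the implementation of this standard of care varies considerably among facilities"; the resource guide may reduce that variation, but nothing is quantified. At a single time point, equal TAU variation removes the error and larger variation reverses it. The claim about TAU intervals is the weaker half, since the three-wave check points the other way.

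Third, counsellors share 40 hours of training, refreshers and supervision, and counselling quality is to be monitored. That may make v small. An active-arm ICC of 0.06 to 0.08 (0.03 plus 0.03 to 0.05) also lies above the 0.025 to 0.040 range the article cites. Larger type I errors can be produced with a facility ICC of 0.01 or with normal reference values. The first departs from the stated 0.03. The second brings in a separate small-sample problem that exists without any counsellor effect.

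Fourth, the stated decision rule is the overall group test, which stayed near 5% in the single-time-point check. This limits the consequence for the trial's headline result, but it does not repair the interval promised for the main contrast.

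**Conclusion.** The point holds conditionally. The structural mismatch is in the document: one counsellor per active facility, none in TAU, one facility effect for all arms and visits, and the two active arms as the main contrast. If counsellors differ, the main interval would be too narrow. With v of 0.01 to 0.05 and a facility ICC of 0.03, its type I error is about 5.4% to 7.4% at a single time point, which is modest. In a literal three-wave model with time-constant intercepts it is considerably larger for change from baseline. The single-time-point result also requires TAU facilities to vary less than active ones. No direction should be claimed for the TAU contrasts. If counsellors do not differ, and the facility variance is otherwise equal across arms and visits, there is no error.

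**What to change.** Amend Primary analyses in one of two ways.

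1. Let the facility variance differ between the active arms (one common value) and TAU, and add a facility-by-time random effect so that it can also change after baseline.
2. Estimate the 12-month Dedicated-versus-Designated contrast from the 16 active clinics only, with t on about 14 df (16 − 2, less one if urban-rural status is fitted).

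Separate variances by arm are not enough alone. In the three-wave model with time-constant intercepts they leave main-contrast type I error at about 5% to 8.5% for 12-month means and 7% to 25% for change from baseline. The second option does not depend on how much TAU facilities vary, and the sponsor need not know the counsellor ICC.

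The cost is a sentence or two of text and a model option. If there is no counsellor effect, power at 40 completers per facility falls from 71% to 69% for a 2-unit AUDIT difference, and from 96.5% to 95.6% for 3 units.

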### Study sites: selection and randomisation

The trial will be conducted at 24 co-located HIV and diabetes treatment clinics in the Western Cape. For these clinics to be included in the trial, they needed to treat large enough numbers of patients to facilitate patient recruitment and be co-located within PHC facilities. For the most part, HIV and diabetes services are provided by separate, vertically organised clinics co-located within the same PHC facility; this study requirement therefore is unlikely to introduce a selection bias. The WCDOH purposively selected PHC facilities to participate in the trial. Selected facilities vary in size and the extent to which comprehensive health services are provided in order to be broadly representative of the mix of PHC facilities available in the province. Facilities are located in most of the health districts in the province, with 15 being urban and 9 being rural sites. This urban: rural ratio is reflective of the provincial distribution of PHC clinics.

An independent statistician will conduct randomisation after all PHC facilities selected to participate in the trial formally agree to participate. Randomisation will be based on randomly generated numbers (computer based), stratified by urban-rural status. Within each stratum, facilities will be allocated to the three study arms with equal probability (1:1:1 ratio). Specifically, facilities will be assigned a random number between 0 and 1 using the rand() function in Excel. Then these facilities will be sorted in ascending order based on the random numbers, and the first third of facilities will be assigned to the dedicated arm, the second to the designated arm and the last third to the TAU arm.

It is not possible to blind investigators involved in the delivery of the intervention to group allocation. In addition, due to the nature of the intervention, it is not possible to blind the facilities to group allocation. Investigators will be blind to the sequence generation, and all allocations will be concealed until the facility is assigned to a study arm. Further, CHWs delivering the intervention and outcome assessors administering patient questionnaires will function independently of each other: CHWs will not conduct any assessments, ensuring that these assessments remain independent from the counselling sessions and assessors collecting outcome data remain blind to the content of the counselling sessions.

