### Patient recruitment and study procedures

Eligible patients will be at least 18 years of age, take antiretroviral therapy (ART) for HIV or medication for diabetes, screen for hazardous/harmful alcohol use (Alcohol Use Disorders Identification Test (AUDIT) score ≥ 8) or depression (Center for Epidemiology Scale on Depression (CES-D) score ≥ 16), not be currently receiving treatment for a mental health condition, and not be participating in another study.

During the study period, all patients presenting for HIV or diabetes care will be asked about their use of alcohol in the past year and recent low mood by their health care provider. Patients who respond positively to one of these two questions will be referred to an assessor for study eligibility screening. After explaining the purpose of the study, the assessor will request verbal consent to screen the patient for possible study inclusion. If a patient is eligible and interested in participating, the assessor will make an appointment for the enrolment visit. At this visit, the assessor will re-screen the participant for study eligibility prior to obtaining informed consent to participate in the trial. Thereafter the assessor will administer the baseline assessment in either English, Afrikaans or isiXhosa, the three official languages of the Western Cape province. This computer-assisted personal interview collects socio-demographic information as well as information on HIV disease, adherence and treatment; diabetes disease, adherence and treatment; CMDs; patterns of health service use and associated patient costs; self-efficacy; readiness to change; problem-solving styles; social support and HrQoL (see Fig. 2 for a description of the measures). Next, a registered nurse will draw up to 10 ml of venous blood to assess the participants’ HIV viral load and HbA1c levels, as appropriate. The blood samples will be sent to a local accredited laboratory for analysis. The assessor will then schedule counselling appointments for participants recruited from facilities assigned to the intervention arms. Ideally, the first session will take place within 3 days of the enrolment visit, with the remaining two sessions scheduled 5 days apart. Participants will have 6 weeks from enrolment to complete these three sessions.

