#### Primary outcome measures

All primary outcomes are at the level of the individual patient and will be collected at baseline and the two follow-up assessments.

*Hazardous/harmful alcohol use* as measured by the 12-item Alcohol Use Disorders Identification Test (AUDIT) [47]. The AUDIT has been validated for use among South African patients utilising health care facilities [48].

*Depressive symptomatology* as measured by the Center for Epidemiologic Studies Depression Scale (CES-D), a 20-item scale that measures depressive feelings and behaviours during the past week [49] and has been used to measure change in symptoms of depression among PHC patients [31, 34].

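### The primary model names no baseline-score adjustment, so a 12-month contrast leaves precision unused and passes on recruitment imbalance; a change contrast would also need a facility-by-visit effect

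*Protocol article*

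**What the plan says.** The Primary analyses section of the protocol article sets out the model: "Mixed-effect linear regression models will be used with clusters and participants specified as random effects". It goes on: "The two primary outcomes will be ascertained at three time points for each participant". The Primary outcome measures section says that these outcomes "will be collected at baseline and the two follow-up assessments", so baseline is one of the three occasions. The target is the arm contrast at the last visit: "This repeated measure feature will be used to estimate the intervention effects and 95% confidence intervals for the two primary outcomes at 12 months". On covariates it says: "Our primary analysis of outcomes will include adjustment for stratification variables". Under Study sites: selection and randomisation, the only stratification factor is urban-rural status. The section names neither a baseline covariate nor a facility-by-visit term, and does not say whether baseline arm means are constrained to be equal.

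Sample size considerations puts the comparison on mean AUDIT and CES-D scores at 12 months.

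On recruitment, the section on study sites says that "it is not possible to blind the facilities to group allocation". Providers make the first referral, and the Discussion acknowledges the reliance on facility staff. The person who enrols a patient also acts on the allocation: "The assessor will then schedule counselling appointments for participants recruited from facilities assigned to the intervention arms". Trial status dates cluster enrolment from 19 April and participant enrolment from 17 May 2017.

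**The concern.** In a cluster trial, randomising facilities does not balance patients who are recruited afterwards by people who know the arm. Here recruitment probably follows allocation, facilities are open to it, and entry is by either of two routes (AUDIT of 8 or more, or CES-D of 16 or more). The mix of entrants therefore drives a facility's mean AUDIT at baseline. Adjusting for urban-rural status does nothing about that.

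The baseline score is the obvious remedy and is already collected. Listing baseline as a modelled occasion does not by itself adjust for it. With free arm means at every visit, complete data and the random effects named, the fitted 12-month arm difference is simply the raw 12-month difference.

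If the effect is instead read as a difference in change, baseline is used, but a different problem arises. The facility intercept cancels from the change, and the model has no term for facilities moving differently over time. Its standard error would then be too small wherever such movement exists.

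**Working it through.** **1. The plan's own figure.** Inputs from Sample size considerations: two-sided α 0.05, 90% power, ICC 0.03, 20 analysed per cluster, AUDIT difference 3 with SD 6.5, CES-D difference 5 with SD 10.
- Design effect = 1 + 19 × 0.03 = 1.57.
- AUDIT: 2 × (1.96 + 1.2816)² × (6.5/3)² = 98.65 per arm; × 1.57 / 20 = 7.74, so 8 clinics.
- CES-D: 84.06 per arm; × 1.57 / 20 = 6.60, so 7 clinics.
- Attrition: 20 / 0.8 = 25, and 24 × 2 × 25 = 1200.

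All stated figures reproduce. No baseline covariate enters them.

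**2. The 12-month level contrast: precision.** Work in SD units, with r the assumed within-person correlation between baseline and 12 months (not given in the protocol).
- Variance of a facility mean, unadjusted: 0.03 + 0.97/20 = 0.0785.
- Adjusted for the participant's baseline: 0.03 + 0.97 × (1 − r²)/20. This leaves the between-facility part untouched, so it is cautious.
- SE of the contrast = √(2/8 × variance). Standardised AUDIT effect = 3/6.5 = 0.4615. Power is from the noncentral t on 20 df (24 facilities less 3 arms and 1 stratum term).

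| r | variance | reduction | SE | AUDIT power |
|---|---|---|---|---|
| none | 0.0785 | – | 0.140 | 88% |
| 0.3 | 0.0741 | 6% | 0.136 | 90% |
| 0.5 | 0.0664 | 15% | 0.129 | 93% |
| 0.7 | 0.0547 | 30% | 0.117 | 96% |

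The unadjusted 88% differs from the 90.9% given by the plan's normal approximation only through the t reference. If baseline facility means also explain between-facility variation, the gain is larger: the SE falls by 7 to 41% over r = 0.3 to 0.7 and cluster autocorrelation 0.5 to 1.

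**3. The 12-month level contrast: imbalance.** A baseline difference of D points between arms carries over as about r × D. For D = 1 AUDIT point (assumed), this is 0.3, 0.5 or 0.7 points at r = 0.3, 0.5 or 0.7; divided by 3, that is 10, 17 or 23% of the target. Simulated type I error for this contrast, without imbalance, stayed near nominal (3.8 to 6.0%).

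**4. The change contrast.** Let c be the cluster autocorrelation (assumed), with r = 0.5 and m patients per facility. The facility-by-visit variance is s = 0.03 × (1 − c), and the within-person residual is e = 0.5 − s.
- True variance per facility is proportional to s + e/m.
- The intercept-only model takes it as (s + e)/m = 0.5/m.
- Example, c = 0.8, m = 20: s = 0.006, e = 0.494; true 0.006 + 0.0247 = 0.0307; model 0.025; SE ratio √(0.0307/0.025) = 1.108; type I error = 2 × [1 − Φ(1.96/1.108)] = 7.7%.

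| c | m = 20 | m = 40 |
|---|---|---|
| 1.0 | 5.0% | 5.0% |
| 0.9 | 6.3% | 7.8% |
| 0.8 | 7.7% | 10.6% |
| 0.5 | 11.8% | 18.3% |

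Simulations of 4000 null trials agree: about 6 to 12% at 20 per facility and 8 to 19% at 40 for c from 0.9 to 0.5, and about 5% at c = 1. The 40 column applies only if HIV and diabetes patients are analysed together; the sample size is built on separate analyses at 20.

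**The case against.** The strongest reply is that this is a condensed article, and that covariate lists, mean structure and degrees of freedom usually sit in the analysis plan. The text says adjustment will include stratification variables, which does not exclude others. A reader might infer that baseline adjustment has been ruled out; the document does not say so. The moderator section adds baseline AUDIT category as a further factor, which suggests that it is not already in the primary model but does not prove it. What remains is that the article fixes the occasions, the random effects, the time of the contrast and one adjustment. Followed as written, they leave the baseline score out of the 12-month contrast.

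A reader might also infer that unused baseline data, uncorrected imbalance and too-small standard errors all afflict one model. They do not. The first two belong to the level contrast, where type I error is near nominal. The third belongs to the change contrast, which uses baseline and over-corrects an imbalance by about (1 − r) × D. The sample size section favours the level contrast; wording elsewhere about reductions and change is looser and specifies no change test.

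Nor do the documents show that type I error is inflated. They give no cluster autocorrelation, and without drift the error is 5%. The Discussion says only that other initiatives and contextual differences may affect findings.

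The size of any baseline imbalance is likewise unknown. All presenting patients are asked the same two questions and eligibility uses fixed cut-offs, which limits selection without removing it. The order of randomisation and patient enrolment is likely but not stated outright.

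Finally, with up to 20% attrition, a likelihood model containing baseline does use it for participants who miss the 12-month visit. The statement that baseline adds nothing therefore holds strictly for complete data.

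**Conclusion.** The point stands as a worthwhile improvement to the primary model. For the 12-month level contrast with free baseline arm means, the stated model forgoes a variance reduction of about 6 to 30% (AUDIT power about 88% against 90 to 96%) and leaves in place a bias of about r × D. Both results rest on assumed r of 0.3 to 0.7, and the bias also on an assumed D. A reader might conclude that the trial is underpowered by its own standard; it is not, because the planned size ignores baseline and reproduces. The type I error concern is conditional: it needs a change contrast and facility means that drift, neither of which the protocol establishes.

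**What to change.** State that the primary estimand is the arm difference in level at 12 months. Model the 6- and 12-month scores as outcomes, with fixed effects for arm, visit, arm × visit, urban-rural stratum and the participant's baseline score. Include random effects for facility, facility × visit and participant, and use Kenward-Roger or Satterthwaite degrees of freedom for the 12-month contrasts.

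Prefer baseline as a covariate to a model that constrains baseline arm means to be equal. The constrained model would also recover the precision, but it assumes equal expected baseline means, which recruitment after allocation may break.

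The cost is a change of wording, using data already collected. The small drawback is that the facility × visit variance may be poorly estimated with 24 facilities.
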